### Study design

This RCT comprises 1) an effect evaluation, 2) a cost-benefit analysis, and 3) a qualitative evaluation. The main focus of the study is the effect evaluation. The cost-benefit analysis is included to evaluate the resources invested in the intervention, compared to the potential economic gain from reduced sickness absence and increased labor market activity. The qualitative evaluation is conducted to gain insight into stakeholder’s experiences.

### Effect evaluation

The effect evaluation is a RCT, which is ideal for the aim of comparing interventions to increase RTW of sick listed individuals. See Fig. 1 for study flow.

**Fig. 1 Fig1:**
[figure not shown]
Study flow

### Interventions

The procedure is organized by NAV. By a randomization procedure, eligible participants are allocated to the IME or TAU. The IME procedure is developed in cooperation with the Research Unit for General Practice at Uni Research Health, and NAV.

Two weeks in advance of the IME consultation, NAV sends an appointment notice to the IME participant, and a request to his/her personal GP to send a medical summary to inform the IME physician. The GP is payed a fixed rate for this summary. The IME physician has a total of 2 h for preparation, consultation (30–60 min) and for writing an IME report. The IME report is sent to the patient, the patient’s GP and NAV. The report will primarily serve as a tool for the GP’s continued follow-up of the patient. The IME report provides a second opinion on the patient’s fitness for work or need for continued sick leave, full or graded. The GP may use this evaluation in his/her communication with the patient, particularly if the IME report points at new options for treatment or other initiatives. The GP is responsible for further follow-up actions and sick leave certificates. Both the intervention group and control group receives TAU (regular follow-up in Norway), which is described in the background section. There are no restrictions in participation in concomitant care or interventions during the study.

Specially trained GPs (the IME physicians) are temporarily employed by NAV to perform the IME consultations. The IME physicians were recruited through job announcements. GPs were required to have a minimum of 3 years clinical practice, with completed or ongoing specialization in general practice. As a main rule, the IME physicians use their own offices for the IME consultation. The training of the IME physicians consisted of a 1-day course (7 h) with information about the project, lectures on basic risk factors for LTSA and the GP’s role in the sickness certificate process. The most important themes were addressed by casuistry and lectures of peers and social security stakeholders covering the complexity of illness, sickness, disease, functional ability, and work ability. Dilemmas of GP’s dual roles as gatekeeper and the patient’s advocate were discussed. Essential in the lectures were knowledge on health effects of working when sick, the Norwegian model of an inclusive working life, and the important role of the employer and the work place in relation to the sick-listed employee. In depth information about the Norwegian social security legislations and work-related actions within the NAV system was included in the lectures. Furthermore, the IME physicians learned about the specific procedures necessary to perform the IME. This included training in using the NAV database in order to get access to information about patients. A second, 3-h training session for the IME physicians was held after a 4-week pilot-period. IME physicians participating in the pilot shared their experiences with the other IME physicians and they all received training in practical and technical procedures.

A third, 4-h training session with the IME physicians was held 4 months after project start. Prior to this, two specialists in the field assessed three IME reports for each of the physicians, and gave written, specific feedback. At the third session the feedback was discussed with the IME physicians individually. Rest of the session was used for group discussions.

As a framework for themes addressed in the IME consultation, the IME physician use a report form. Before meeting the patient, the IME physician prepares for the consultation by starting to fill out the report form with background information from the NAV database and the GPs summary. The IME report includes the following information:Name of IME physicians, date of consultation, name of patient, national identity number and a check box for whether the patient did meet or not for the IME consultation.Name of the responsible NAV office, name of the patient’s GP and a check box for whether the GP did send a medical summary or not in advance of the IME consultation.Brief background information of the patient’s case history: Date of when the current sick leave started, any specialist report enclosed and grade of sick leave at the time of the IME.Information from the patient on work-related actions carried out during the current sick leave period (partial work, “a faster RTW” - actions, dialogue meetings, other work-related actions).The patient’s resources towards RTW (having an employer, type of occupation, type of work tasks, manageable work tasks for the time being, manageable work tasks if adjustments at the workplace, manageable tasks at home).The patient’s own descriptions of why the work ability is reduced related to medical reasons (somatic, mental, cognitive), practical reasons (waiting for medical elucidations or treatment), specific work tasks at the current work place (tasks that can be done or not, and possibilities of adjustments), work tasks at the labor market in general (unemployed, competences).The patient’s own thoughts about RTW (full or partial), answered on a six-point check box (within a month, within 3 months, within the first year of sick leave, later, RTW is not likely (expected), no thoughts about RTW).The IME doctors evaluation of RTW (full or partial): What is the most important medical barrier for RTW (somatic, mental, cognitive factors)? What is the most important practical barrier for RTW? What is the mort important cognitive barrier for RTW? What is the most important barrier for RTW at the current workplace? Will a change of workplace with similar work tasks make it easier to RTW? Will a change of workplace with new work tasks make it easier to RTW?The IME doctor’s suggestion of actions, which must be justified (explained): Additional medical/psychological elucidation, additional medical/psychological treatment, actions/adjustments at the work place (contact NAV/employer), practical actions (job search, social security benefits), change of work place, dialogue meeting or other actions.The IME doctor must state whether sufficient and adequate actions have been accomplished until the current point of time.The IME doctor must suggest grade of further sick leave from the date of consultation (0–100%).The IME doctors concluding remarks, elaborations and summing up.

### Participants, recruitment, inclusion and exclusion

Participants aged 18–65 years old sick listed by their GP with an ICPC-2 diagnosis are recruited through NAV’s registries, when reaching 22 weeks of sick leave. All sick listed individuals are included, both those with and without an employer. Pregnant women, individuals with secret address, individuals employed by NAV, people with ICD-10 diagnoses (i.e., sick listed by the specialist health services), cancer or dementia are excluded. The goal is to recruit 1900 (1892) participants in each group, with a total sample of 3800 (3784) participants. Sick-listed in other counties serve as an extra control group, if comparison is appropriate under the “common trend” assumption. Included participants are exempt from participation when their treating GP explicitly states that the intervention could worsen the condition.

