**Methods/design:**

The current study is a randomized controlled trial in a Norwegian primary care context, involving an effect evaluation, a cost/benefit analysis, and a qualitative evaluation. Independent medical evaluation will be compared to treatment as usual, i.e., the physicians’ and social insurance agencies’ current management of long-term sick-listed patients. Individuals aged 18–65 years, sick listed by their GP and on full or partial sick leave for the past 6 months in Hordaland county will be included. Exclusion criteria are pregnancy, cancer, dementia or an ICD-10 diagnosis. A total sample of 3800 will be randomly assigned to either independent medical evaluation or treatment as usual. Official register data will be used to measure the primary outcome; change in sickness benefits at 7, 9 and 12 months. Sick listed in other counties will serve as a second control group, if appropriate under the “common trend” assumption.

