## Methods/design

### Aims and objectives

The main aim of this study is to evaluate the effect of IME compared to TAU. The intervention is given to patients after 6 months of continuous sick leave (full or graded sick leave). The IME is conducted by specially trained GPs, performing the IME consultation at their own GP practice in the Norwegian county Hordaland. The following questions will be addressed:Is IME more effective than TAU in getting people back to work after 6 months of sick leave (measured in sick leave grading and length of absence)?Does IME affect sick leave in the Hordaland county control group, compared to sick listed in other control counties, appropriate to comparison?Is IME cost-effective compared to TAU from a societal perspective?How is the intervention affecting the involved stakeholders?

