### Sample size calculation

According to NAV’s registry for Hordaland county, Norway, in 2008, only 15% of workers who had been sick listed for 6 months were not receiving sickness benefits at 7 months (Statistics Norway’s events database (FD-Trygd)). Table 1 shows sample sizes needed to estimate significant effects for five different effect levels (calculated in the analyze programme Stata, by the command “Power” with a 5% significance level, expected positive effect and power of 80%).

**Table 1 Tab1:** Significance level. As scenario 3 shows, we will be able to discover an intervention effect of 3% if 1892 individuals in two groups participate in the study

	Expected effect level^a^	Sample size
Scenario 1:	Control group: 15% and IME: 16%	16,194 in each group
Scenario 2:	Control group: 15% and IME: 17%	4154 in each group
Scenario 3:	Control group: 15% and IME: 18%	1892 in each group
Scenario 4:	Control group: 15% and IME: 19%	1090 in each group
Scenario 5:	Control group: 15% and IME: 20%	714 in each group

Recent research shows positive effect of strict follow-up of people on sick leave in Norway [12, 13]. One RCT from Denmark [14] shows weak or no effect by increased follow-up on sick leave. These studies have been conducted on different groups, with different aims and measures different outcomes. Therefore, we cannot conclude on what can be viewed as a weak/moderate/strong effect. However, we do not expect a negative effect. This reduces necessary sample size compared to studies where the effect can be both positive and negative. We base our inclusion on scenario 3 (Table 1), and aim at recruiting at least 1900 participants to each group.

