### Randomization

When registering eligible participants, trained personnel at NAV contacts a research technician at Uni Research Health by e-mail, stating only the participant’s ID-number, year of birth and gender. The participant is then allocated to one of two groups by use of a computer-generated randomization list.

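### The 15% control rate behind 1892 per group is for people already sick-listed 6 months, but recruitment is at 22 weeks, so the stated 80% power is not supported

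*Protocol article*

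**What the plan says.** All references are to the protocol article.

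- **Recruitment** (Participants, recruitment, inclusion and exclusion): participants "are recruited through NAV’s registries, when reaching 22 weeks of sick leave". The target is 1900 (1892) per group.
- **Allocation** (Randomization): "When registering eligible participants, trained personnel at NAV contacts a research technician at Uni Research Health by e-mail"; "The participant is then allocated to one of two groups by use of a computer-generated randomization list". No week of sick leave is given.
- **Notice** (Interventions): "Two weeks in advance of the IME consultation, NAV sends an appointment notice to the IME participant". The control group has no consultation and so no such notice.
- **Intervention** (Aims and objectives): "The intervention is given to patients after 6 months of continuous sick leave". The closing paragraph of the Background places the consultation at 6 months.
- **Abstract** (Methods/design): people "on full or partial sick leave for the past 6 months" are included.
- **Control rate** (Sample size calculation): "only 15% of workers who had been sick listed for 6 months were not receiving sickness benefits at 7 months". Scenario 3 of Table 1 sets 15% against 18%, with a 5% significance level, a positive effect expected and 80% power, and gives 1892 per group.

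**The concern.** The control rate and the recruitment rule appear to describe different populations. The 15% is a one-month exit rate, from month 6 to month 7, among people who have already lasted 6 months. People recruited at 22 weeks and allocated at registration have about four more weeks in which to leave sick leave before they reach that point. Nothing in the sample size section allows for them: the 1892 computed for people at 6 months is used unchanged as the number to recruit.

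The stated power depends on this. If everyone randomised is analysed, the control proportion at 7 months is higher than planned, and a proportion nearer one half has a larger variance. In addition, people who leave before the consultation cannot benefit from attending it, which dilutes the difference. The one way to make the 15% apply to people allocated earlier is to analyse only those still sick-listed at 6 months, and that would select on an event after randomisation.

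**Working it through.** **1. When does allocation happen?** Six months is about 26.1 weeks and seven months about 30.4 weeks. Allocation must come before the appointment notice, which precedes the consultation by two weeks. A consultation at about week 26 therefore needs allocation by about week 24; allocation on recruitment would be at week 22. If allocation waited until week 26, the consultation could not come before week 28, about two weeks before the 7-month measurement. Most of the text thus points to allocation before 6 months. The abstract points the other way.

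**2. Reproduce the plan's figure.** One-sided 5% test of two proportions, pooled variance, no continuity correction:

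n = [(1.645·s0 + 0.8416·s1) / (p2 − p1)]², where s0 = √(2·p̄(1 − p̄)) and s1 = √(p1(1 − p1) + p2(1 − p2)).

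With p1 = 0.15, p2 = 0.18, p̄ = 0.165: s0 = 0.5249, s1 = 0.5245, and n = (0.8634 + 0.4414)² / 0.0009 = 1892 per group. Power at 1892 is 80.0%. The other rows of Table 1 reproduce as 16,195, 4154, 1090 and 714, against 16,194, 4154, 1090 and 714 printed. The arithmetic is right on its inputs.

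**3. Allow for early exits.** Let e be the share leaving benefit between allocation and 6 months. The document does not give it; I take 2% to 15% as an assumed range. As a benchmark only, applying the 15% monthly rate backwards gives 1 − 0.85^(2.1/4.35) = 7.5% from week 24 and 1 − 0.85^(4.1/4.35) = 14.2% from week 22. I assume that early leavers are still off benefit at 7 months.

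- Control proportion at 7 months: pC = e + (1 − e)·0.15.
- (a) Full difference kept: pT = pC + 0.03.
- (b) Effect only in those who reach 6 months: pT = e + (1 − e)·0.18, so the difference is 0.03·(1 − e).
- Power = Φ[((pT − pC)·√n − 1.645·s0) / s1], n = 1892.

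Example for (b), e = 10%: pC = 0.235, pT = 0.262, s0 = 0.6111, s1 = 0.6108. Then (0.027 × 43.50 − 1.645 × 0.6111) / 0.6108 = 0.277, and power is 61%.

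| e | pC | Power (a) | n per group for 80% (a) | Power (b) | n per group for 80% (b) |
|---|---|---|---|---|---|
| 0% | 15.0% | 80% | 1892 | 80% | 1892 |
| 2% | 16.7% | 77% | 2045 | 76% | 2126 |
| 5% | 19.3% | 74% | 2259 | 70% | 2496 |
| 10% | 23.5% | 69% | 2576 | 61% | 3167 |
| 15% | 27.8% | 65% | 2843 | 53% | 3917 |

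**4. A different effect scale.** The planned odds ratio is (0.18/0.82) / (0.15/0.85) = 1.24. If it applied to the whole period from allocation, pT would be 20.0%, 22.9%, 27.6% and 32.3% for e = 2%, 5%, 10% and 15%, and power would be 83%, 86%, 90% and 92%.

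**5. Restricting to those still sick-listed at 6 months.** With 15% against 18% and 1892·(1 − e) per group, power is 79%, 78%, 76% and 74% for the same values of e, before any selection bias is considered.

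**The case against.** The strongest reply is that the week of randomisation is inferred. Recruitment through a register at 22 weeks could mean identification only, with allocation later. If allocation took place at or after 6 months, as the abstract's wording allows, the 15% would fit and no problem would arise. That stands as a limit on the point. It does not remove the need to state the week, because the notice and a consultation at 6 months cannot be squared with allocation at 6 months.

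A second reply is that lower power is not certain. The early exit rate is unknown, and a constant odds ratio from allocation would raise power above 80%. This also stands. However, that case needs an effect before the consultation, for example through the notice, whereas Table 1 is built on absolute differences. The target is also worded as at least 1900 per group, so it is not a cap.

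Two stronger readings are tempting and not supported. A reader might infer from the abstract and aims that only people still sick-listed at 6 months will be analysed. Those sections give an inclusion criterion and the timing of the intervention; neither defines an analysis set, and an article may leave that to the full protocol or analysis plan. A reader might also put a figure on the bias such a restriction would cause. With 14% early leavers and 2% of the IME arm prompted to leave early by the notice, (0.15 × 0.86 − 0.02) / 0.84 = 13.0% against 15%, a bias of 2.0 points. That holds only if all of those 2% would otherwise have left between months 6 and 7. If they were a random draw of those still sick-listed, the conditional rate would stay at 15% and the bias would be zero.

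**Conclusion.** The point holds as a mismatch between the population that supplies the control rate and the population apparently randomised. The sample size arithmetic is not in error. On Table 1's absolute-difference scale, with all randomised analysed and 2% to 15% assumed to leave before 6 months, the power of 1892 per group is about 77% to 65% with the 3 points kept and 76% to 53% with the effect confined to those who reach 6 months. These figures rest on three assumptions: allocation before 6 months, the assumed exit range, and early leavers staying off benefit until month 7. The document supports no single figure for true power. What can be said is that the stated 80% does not follow from a rate measured in people at a later point of sick leave than the one at which they seem to be allocated.

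**What to change.** - State the week of sick leave at which randomisation takes place, and reconcile the abstract, the Aims and objectives and the Participants section on timing.
- Tabulate from the NAV register the share off benefit at 7 months among people who meet the trial's eligibility criteria at that same week, with its exclusions applied.
- Restate the power, or the detectable difference, for 1900 per group from that rate, and say whether the expected effect includes any return to work before the consultation.
- Keep everyone randomised in the primary analysis, whether or not they are still sick-listed at 6 months or attend. Restricting it to those who reach 6 months would condition on an event that the notice, sent only to the IME arm, could affect. The complete register follow-up makes the full analysis feasible.

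The cost is one register tabulation and some rewording. On the absolute-difference scale the restated power will probably be less favourable, or the target will have to rise.

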### Sample size calculation

According to NAV’s registry for Hordaland county, Norway, in 2008, only 15% of workers who had been sick listed for 6 months were not receiving sickness benefits at 7 months (Statistics Norway’s events database (FD-Trygd)). Table 1 shows sample sizes needed to estimate significant effects for five different effect levels (calculated in the analyze programme Stata, by the command “Power” with a 5% significance level, expected positive effect and power of 80%).

**Table 1 Tab1:** Significance level. As scenario 3 shows, we will be able to discover an intervention effect of 3% if 1892 individuals in two groups participate in the study

	Expected effect level^a^	Sample size
Scenario 1:	Control group: 15% and IME: 16%	16,194 in each group
Scenario 2:	Control group: 15% and IME: 17%	4154 in each group
Scenario 3:	Control group: 15% and IME: 18%	1892 in each group
Scenario 4:	Control group: 15% and IME: 19%	1090 in each group
Scenario 5:	Control group: 15% and IME: 20%	714 in each group

Recent research shows positive effect of strict follow-up of people on sick leave in Norway [12, 13]. One RCT from Denmark [14] shows weak or no effect by increased follow-up on sick leave. These studies have been conducted on different groups, with different aims and measures different outcomes. Therefore, we cannot conclude on what can be viewed as a weak/moderate/strong effect. However, we do not expect a negative effect. This reduces necessary sample size compared to studies where the effect can be both positive and negative. We base our inclusion on scenario 3 (Table 1), and aim at recruiting at least 1900 participants to each group.

### Subgroups

Subgroup analyses of effects can be performed if sample size allows this. A priori, the following variables are particularly relevant for a subgroup analysis: age groups, gender, education, main diagnosis group and geographical location.

### Randomization

When registering eligible participants, trained personnel at NAV contacts a research technician at Uni Research Health by e-mail, stating only the participant’s ID-number, year of birth and gender. The participant is then allocated to one of two groups by use of a computer-generated randomization list.

### Qualitative evaluation

In order to investigate stakeholder’s experiences with the project, and how it affects them and the relation between them, two qualitative studies will be conducted. We will conduct semi-structured individual interviews with patients after attending an IME consultation and focus groups with GPs who have patients who attended an IME consultation. Topics discussed in the interviews and focus groups will relate to the stakeholder’s views of what changed/did not change the sick leave and/or follow-up after the IME consultation.

## Discussion

The effect evaluation of an independent medical evaluation (IME) after 6 months sick leave is a large RCT, providing evidence on the effect of IME on RTW after LTSA. It is the first controlled evaluation of IME.

## Abbreviations

GP: General practitioner
HELFO: The Norwegian Health Economics Administration
IME: Independent medical evaluation
LTSA: Long-term sickness absence
NAV: The Norwegian Labour and Welfare Administration
